### Statistical analysis of phase II

Phase II analysis will be performed according to the intention-to-treat strategy. Analyses will be performed separately for the two planned comparisons. In each comparison, TRG1 rate is defined as the rate of patients out of those randomized who will experience a complete pathological regression according to Mandard modified scoring system (responders). Patients who will not achieve a TRG1 will be defined as non-responders. Patients who will not undergo primary surgery because of progressive disease will be defined as non-responders. TRG1 rates will be compared with chi-square test in a 2×2 contingency table (responders/non-responders x treatment arms).

For each patient and for each type of toxicity, the worst degree suffered during treatment will be used for the analysis. Two sets of statistical analyses will be performed to compare toxicity. In the first set the whole pattern of toxicity (all grades) will be considered for each item; analysis will be done by a linear rank test. In the second set toxicity will be defined as severe (mostly including grade 3 or higher) and not severe (mostly including grades up to 2) and analysis will be performed by Fisher’s exact test.

Due to the small sample size, statistical analysis of biomarkers data will be conducted with the aim of hypothesis generation. Biomarkers that might change over time as a consequence of treatment, levels before and after treatment will be compared with appropriate statistical tests, based on the type of data.

QoL will be described according to EORTC rules
[58, 59].

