#### Phase II

The randomized phase II multicentre study will have two distinct time windows: the first one while phase I studies are ongoing and the second one after phase I studies have defined the RP2D of capecitabine (C) without and with VPA (V- and V+) (Figure 
1b).

In the first window, randomization will be 1:1 to 2 arms, SCRT and V/SCRT, with patients randomized when a phase I slot is not available at the time of their inclusion. Its duration depends on the duration of phase I studies and there is no definite sample size.

In the second window, randomization will be 1:1:1:1 to 4 arms: SCRT; V/SCRT; C/SCRT CV/SCRT (Figure 
1b).

The primary endpoint of the phase II study is the TRG1 rate according to Mandard modified scoring system
[45], after definitive surgery.

We will conduct the randomized phase II study, with two separate comparisons, according to the following scheme:to test the effect of capecitabine: SCRT + V/SCRT vs C/SCRT + CV/SCRT;to test the effect of VPA: SCRT + C/SCRT vs V/SCRT + CV/SCRT.

Sample size for phase II study is calculated for the second time window. In details, a sample size of 86 patients (approximately 21–22 pts assigned to each arm) is planned under the hypothesis that the addition of capecitabine or VPA to SCRT can improve the TRG1 rate from 5% to 20%, with one-sided alpha = 0.10 (that is 0.20 corrected for the 2 planned comparisons) and 80% power. Patients randomized during the first time window, will be added to the analysis of the effect of valproic acid; as a consequence, the statistical power of such comparison will be increased and more reliable estimates of treatment toxicity will be produced. Randomization will be performed with a minimization procedure that will account for centre, clinical N stage (N0 vs N1) and clinical T stage (T2 vs T3).

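### The primary TRG1 test is a crude 2×2 chi-square that leaves out cT, cN and the other factorial drug: valid, but slightly inefficient, and it needs its one-sided level and uncorrected form stated

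*Protocol article*

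**What the plan says.** The protocol article's section on statistical analysis of phase II fixes the primary test: "TRG1 rates will be compared with chi-square test" in a 2×2 table, with responder status as one dimension and treatment group as the other. The two planned comparisons are analysed separately, with all randomised patients in the denominator. The section names no stratification factor, direction, test level or continuity correction.

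The Phase II part of the study design section gives the features that the test has to serve:
- Allocation uses a "minimization procedure that will account for centre, clinical N stage (N0 vs N1) and clinical T stage" (T2 vs T3).
- "In the second window, randomization will be 1:1:1:1 to 4 arms". Each drug is tested on a factorial margin, that is, the two arms with it against the two arms without it.
- A first window randomises 1:1 between SCRT alone and SCRT with VPA. Its patients join the VPA comparison only.
- "a sample size of 86 patients (approximately 21–22 pts assigned to each arm) is planned", for an improvement in TRG1 from 5% to 20% "with one-sided alpha = 0.10 (that is 0.20 corrected for the 2 planned comparisons) and 80% power".

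**The concern.** The design and the primary test do not use the same information. Stage is balanced at randomisation and then dropped from the analysis. Each margin also mixes patients with and without the other drug, although the sample size hypothesis allows that drug to move TRG1 from 5% to 20%. When a balanced factor that predicts outcome is left out, the crude variance is too large for the allocation used, so the test rejects too rarely under the null and loses some power.

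The second issue is that a 2×2 chi-square statistic carries no sign and comes in corrected and uncorrected forms. With few responders these forms differ materially. Since the level and form are not tied to the test where it is defined, an analyst working from the analysis section alone could run a test with properties other than those planned.

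**Working it through.** **1. Reproduce the plan's sample size.** Inputs from the article: p1 = 0.05, p2 = 0.20, one-sided α = 0.10, power 0.80. Mean rate = 0.125. Pooled-variance formula, no continuity correction:

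n per margin = [z(0.90)·√(2×0.125×0.875) + z(0.80)·√(0.05×0.95 + 0.20×0.80)]² / 0.15²
= [1.2816×0.4677 + 0.8416×0.4555]² / 0.0225 = 42.9, so 43 per margin and **86 in total**.

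Power at 43 vs 43 = Φ[(0.15×√43 − 1.2816×0.4677)/0.4555] = Φ(0.843) = 80.1% (unrounded 80.05%). The plan's figure is reproduced. This statistic is the signed square root of the uncorrected chi-square, so test and sample size agree if the chi-square is read at p < 0.20 in the favourable direction.

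**2. Other readings of the same test.**
- Two-sided 0.10 (z = 1.6449): power = Φ[(0.9836 − 1.6449×0.4677)/0.4555] = Φ(0.470) = 68.1%. Reaching 80% would take 60 per margin, 120 in all.
- One-sided 0.10 with continuity correction in the sample size formula: 112 patients.

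Exact binomial enumeration, 43 vs 43, rejecting only in favour of the drug:

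| Test | Power, 5% vs 20% | Size, both 5% | Size, both 12.5% |
|---|---|---|---|
| Uncorrected, one-sided 0.10 | 82.6% | 11.9% | 10.2% |
| Corrected, one-sided 0.10 | 72.3% | 2.5% | 5.7% |
| Uncorrected, two-sided 0.10 | 70.9% | 5.7% | 5.1% |
| Corrected, two-sided 0.10 | 57.7% | 0.8% | 2.4% |

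The 5% column is the case where neither drug works (43×0.05 = 2.15 responders expected per margin). The 12.5% column is the case where the other drug gives 20% in half of each margin, (5% + 20%)/2, so 43×0.125 = 5.4 responders.

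An example of the difference: 2/43 vs 6/43 gives p = 0.138 uncorrected and 0.265 corrected. The first passes at one-sided 0.10 (p < 0.20), the second does not.

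**3. Cost of leaving the factors out.** The article gives no prognostic effects, so these are assumptions. An odds ratio of 4.75 corresponds to 5% vs 20%: (0.20/0.80)/(0.05/0.95).

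Simulation A: 100,000 runs, 84 second-window patients in equal cells, one balanced binary prognostic factor. VPA comparison at one-sided 0.10, VPA odds ratio 4.75 under the alternative, no first-window patients:

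| Assumed | Size, crude → CMH | Power, crude → CMH |
|---|---|---|
| No prognostic factor, capecitabine inactive | 11.9% → 11.9% | 82.0% → 82.0% |
| Prognostic OR 3 only | 11.6% → 11.6% | 82.2% → 82.6% |
| Capecitabine OR 4.75 only | 9.6% → 10.0% | 93.3% → 94.2% |
| Both | 9.1% → 10.1% | 92.2% → 93.7% |

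With 40 or 80 first-window patients added and capecitabine active, crude size is 9.1% to 10.1% against 10.1% to 10.4% for CMH, and the power gain is at most 0.4 points.

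Simulation B: 3,000 runs, 86 patients, assumed odds ratios T 1/3, N 1/2, capecitabine 4.75, VPA 3. Size goes from 8.2% to 9.7% and power from 71% to 74%. With stronger prognostic factors, power goes from 70% to 74%.

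Together: about 0 to 4 points of power, and no inflation from the omission.

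**The case against.** The best defence is that test and sample size already agree. The study design section states one-sided 0.10, and 86 is exactly what the uncorrected pooled test needs. Stratification is then a preference about efficiency in a phase II trial that says it is exploratory, and its gain depends on odds ratios that nobody has supplied. Most of this stands, and it limits the point to an improvement.

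Four stronger readings are tempting, and the documents do not support them:
- *The trial has only 68% power.* That holds only if the one-sided level in the design section is set aside and the p-value is held against two-sided 0.10, which the article never says.
- *The crude test is biased or anti-conservative because it ignores the factors.* The simulations show the reverse: it is slightly conservative when the other drug is active.
- *Pooling the first window confounds the VPA effect.* VPA is allocated 1:1 in both windows, and first-window patients enter no other comparison.
- *A stratified test would cure the small-sample error.* With neither drug active and a 5% rate, crude and CMH have the same size, about 12%. A CMH test also has a continuity-corrected form, so the form must be named there too.

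The defence does not remove one thing. The article does not leave the primary test open; it fixes an unstratified one. Nor does it tie the level and the uncorrected form to that test.

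**Conclusion.** The point holds as a modest improvement. The crude chi-square is a valid test and 86 is the right number for its uncorrected one-sided form. Leaving out cT, cN and the other drug loses roughly 0 to 4 points of power and makes the test slightly conservative if the other drug works. That range rests on the assumed odds ratios shown and would be near zero if stage does not predict TRG1 and the other drug is inactive.

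The specification gap could cost more if it were resolved the wrong way: exact power of about 72% with a continuity correction, or 68% (normal approximation) to 71% (exact) at two-sided 0.10, against 80.1% as planned. These are consequences of possible misreadings, not of the plan as its two sections read together.

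Separately, the true size of the uncorrected test is about 12% if the common rate is as low as 5%, and close to nominal (10.2%) at 12.5%.

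**What to change.** In the section on statistical analysis of phase II:
- Make the primary test for each comparison a Cochran-Mantel-Haenszel test without continuity correction, at one-sided alpha 0.10 in the favourable direction, as in the study design section.
- Stratify by the other drug, cT, cN and, for VPA, enrolment window. Leave centre out because the cells would be too sparse.
- Report a Mantel-Haenszel risk difference with its confidence interval.
- Keep the uncorrected crude chi-square at one-sided 0.10 as a sensitivity analysis, and note that true size may be about 12% if the common rate is near 5%.

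The cost is a wording change. All the factors are known at randomisation and N stays at 86. The small downside is sparse strata: 2×2×2 = 8 in the second window, plus 2×2 = 4 in the first for VPA, since no one there receives capecitabine. Strata with no responders add nothing to the test.

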### Objectives

The primary objective of the Phase I study is to determine the MTD of capecitabine given alone or in combination with valproic acid during preoperative SCRT.

The primary objective of the phase II comparative study is to explore whether the addition of valproic acid and/or capecitabine to SCRT before optimal radical surgery might increase the rate pathologic complete tumor regression (reported as tumor regression grade 1; TRG1) in patients with low-moderate risk rectal cancer.

Within each planned phase II comparison, secondary objectives include the evaluation of local control, disease free survival and overall survival, pathological CRM negative (>1 mm) and lymph node negative rate, short and long-term toxicity, surgical complications, and quality of life. The study also aims to validate the predictive role of early tumor metabolic changes measured by positron emission tomography (PET) scan (both phase I and II) and to assess the diagnostic accuracy of pre-surgical rectal biopsy, performed after the induction of anaesthesia in all surgical operations and analysed by intraoperative pathology (both phase I and II).

A translational sub-study is also planned, within the phase II trial, with several aims: (a) to compare the expression of several biomarkers (TP, TS, VEGF, RAD51, XRCC1, Histones and proteins acetylation, HDAC isoforms) in the tumor and normal mucosa, at baseline and at different time points during and after treatment; (b) to analyse polymorphisms of genes that may affect activity and toxicity of chemo-radiotherapy (DPD, TS, XRCC1, GSTP1, RAD51 and XRCC3) on DNA from peripheral blood; (c) to evaluate Circulating Endothelial Cells (CEC) and Progenitors (CEP) counts on peripheral blood at baseline and at different time points during and after treatment; (d) to evaluate Histones and proteins acetylation (H&P-Ac) of PBMCs at baseline and at different time points during and after treatment.

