### Pharmacodynamic, pharmacogenetic and pharmacokinetic studies on tumor and blood samples

Tumor and normal mucosa samples will be collected only in patients enrolled in the four-arm phase II study: at baseline (possibly within the diagnostic rectal biopsy) and at surgery for all patients and at day -4 in patients assigned VPA.

Baseline tumor expression of TP, TS, VEGF, RAD51 and XRCC1, will be compared with normal mucosa and with tumor expression at the following time points as pharmacodynamic/predictive markers of treatments (analyzed by real-time PCR and immunohystochemistry). In fact, as reported above, several evidences, by our group and others, including preliminary results, suggested a crucial role of the modulation of the expression of TS and TP in the synergism observed between HDACi and fluoropyrimidine. On the other hand, TP showed a strong sequence homology to the pro-angiogenic platelet derived endothelial cell growth factor (PD-ECGF), and may contribute to angiogenesis, tumor progression and metastasis. However, several reports have clearly shown that HDACi inhibit tumor-induced angiogenesis by regulating VEGF production and signaling. Moreover, the expression DNA repair genes, such as RAD51 or XRCC1, affecting sensitivity to RT and or chemotherapeutics, can be also regulated by HDACi.

Histones and proteins acetylation (H&P-Ac) measured at all the time points and HDAC isoforms evaluated at baseline represent additional pharmacodynamic/predictive specific markers of VPA HDACi activity.

Peripheral blood samples will be collected at baseline, on day -4, 1, 8, 11, 22 and at surgery. VPA serum level will be measured by a valproate test at all time points and correlated with H&P-Ac, measured on peripheral PBMC as additional surrogate pharmacodynamic markers of VPA activity by multiparametric flowcytometry.

Polymorphisms of genes that may affect activity and toxicity of radio-chemotherapy such as DPD, TS, XRCC1, GSTP1, RAD51 and XRCC3, will be analyzed on baseline samples by pyrosequencing technology.

Circulating Endothelial Cells (CEC) and Progenitors (CEP) counts will be analyzed as surrogate marker of tumor angiogenesis at baseline, on day 1, 11 and at surgery by multiparametric flowcytometry.

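### Biomarker change is planned as a before/after comparison; once radiotherapy has begun this cannot separate VPA or capecitabine effects from radiotherapy and time, although randomised controls are sampled

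*Protocol article*

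**What the plan says.** In the protocol article, the section 'Statistical analysis of phase II' states that "statistical analysis of biomarkers data will be conducted with the aim of hypothesis generation", giving small sample size as the reason. For "Biomarkers that might change over time as a consequence of treatment" the analysis is that "levels before and after treatment will be compared with appropriate statistical tests, based on the type of data". The type of test is left open, but the contrast is named: before against after. In the same section TRG1 is compared by treatment arm with a chi-square test, and toxicity has its own comparative tests.

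Other sections use the same time contrast. 'Objectives' sets out to compare tissue markers "in the tumor and normal mucosa, at baseline and at different time points during and after treatment". The section on pharmacodynamic, pharmacogenetic and pharmacokinetic studies compares baseline tumour expression with normal mucosa and "with tumor expression at the following time points as pharmacodynamic/predictive markers of treatments". That section also plans one analysis of another kind: VPA serum level is to be correlated with histone and protein acetylation in PBMCs.

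On sampling, "Peripheral blood samples will be collected at baseline, on day -4, 1, 8, 11, 22 and at surgery", with no restriction by arm. CEC and CEP counts "will be analyzed as surrogate marker of tumor angiogenesis at baseline, on day 1, 11 and at surgery". Tumour and normal mucosa are taken at baseline and surgery in all patients of the four-arm study, and at day -4 only in patients assigned VPA.

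**The concern.** The translational work is meant to show pharmacodynamic activity of VPA and to add insight into how VPA, capecitabine and radiotherapy interact. That requires telling the three apart. Every randomised arm receives the same 25 Gy, so a within-patient change after radiotherapy starts contains whatever radiotherapy, elapsed time, assay drift and regression to the mean contribute, plus any drug effect. A before/after test asks whether the marker moved. It does not ask whether the drug moved it.

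The design already supplies what would answer the second question: 1:1:1:1 allocation with an SCRT-alone arm, and samples listed at common times. If only the before/after results are reported, hypotheses about VPA or capecitabine may be generated from changes that would have occurred without either drug.

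**Working it through.** **1. Group sizes.** The plan's own figure is 86 patients (TRG1 5% versus 20%, one-sided alpha 0.10, 80% power). With pooled variance and no continuity correction, n per side = [1.2816 × √(2 × 0.125 × 0.875) + 0.8416 × √(0.05 × 0.95 + 0.20 × 0.80)]² / 0.15² = (0.599 + 0.383)² / 0.0225 ≈ 43, so 86 in total. The figure reproduces. It serves here only to fix group sizes: 43 per side of each factorial comparison and 21–22 per arm. The article gives no SD or power for any biomarker.

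**2. What each sample can show.** VPA runs from day -14 to day 21. Radiotherapy is given on days 1 to 5. Capecitabine starts with radiotherapy or the day before. Surgery is 8 weeks after the last radiotherapy day: 5 + 56 = day 61, which is 61 − 21 = 40 days after the last VPA dose.

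| Sample | VPA given by then | Radiotherapy begun | Patients without VPA sampled |
|---|---|---|---|
| Tumour and mucosa, day -4 | yes | no | no |
| Blood, day -4 | yes | no | listed without arm restriction |
| Blood, days 8, 11, 22 | yes | yes | listed without arm restriction |
| Blood, surgery | stopped about 40 days before | yes | listed without arm restriction |
| Tumour and mucosa, surgery | stopped about 40 days before | yes | yes, all patients |

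The article does not say whether day 1 blood precedes the first fraction. No sample isolates capecitabine within a patient, because it and radiotherapy start together.

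**3. The two contrasts.** From day 8 on, and ignoring interaction:
- change with VPA and SCRT = VPA effect + radiotherapy effect + time effect;
- change with SCRT alone = radiotherapy effect + time effect;
- the difference between them = VPA effect.

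The same holds for capecitabine. The before/after test examines the first line, and the randomised comparison examines the third.

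**4. Illustrative size.** Assume no drug effect, normally distributed changes and a common shift of d SD of the change. The range of d is an assumption; the article gives no figure. The paired test has noncentrality d√n (for n = 21 and d = 0.5: 0.5 × 4.583 = 2.29). Chance of p < 0.05 (two-sided), confirmed by 20,000 simulated trials:

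| d | Before/after, n = 21 | Before/after, n = 43 | Between groups, either size |
|---|---|---|---|
| 0 | 5% | 5% | about 5% |
| 0.3 | 26% | 48% | about 5% |
| 0.5 | 59% | 89% | about 5% |
| 0.8 | 94% | 99.9% | about 5% |

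**5. Price in precision.** The smallest shift detectable with 80% power at two-sided 5% is approximately (1.960 + 0.842) × √(2/n) between groups and (1.960 + 0.842) × √(1/n) within a group. At n = 43 per side that is 0.60 against 0.43 SD of the change; at n = 21 it is 0.86 against 0.61.

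**The case against.** The case on the other side has five parts, and much of it stands.

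- **Before/after is not the only analysis.** The correlation of VPA serum level with PBMC acetylation is an exposure–response analysis specific to VPA. This is correct, but it covers one marker and one drug.
- **Day -4 is free of radiotherapy.** This is correct: a baseline to day -4 change cannot be a radiotherapy effect. Time, assay and repeat-biopsy effects remain, the tumour sample has no concurrent control, and the window does not reach capecitabine.
- **An arm comparison may be intended.** The section opens with "Analyses will be performed separately for the two planned comparisons", and the full protocol or SAP may hold detail. That sentence is not tied to biomarkers, and the biomarker sentence itself names a time contrast. Nothing excludes an arm comparison, but nothing states one.
- **The percentages are not error rates of the stated test.** This is correct. If radiotherapy really moved the marker, rejecting no change is the right answer. It becomes an error only when the change is attributed to a drug.
- **The analysis is hypothesis-generating.** This lowers the stakes and excuses limited power. It does not make the contrast informative about the drug.

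A reader might infer that radiotherapy effects will be credited to VPA or capecitabine. The article does not say so. It refers to consequences of treatment, and treatment includes SCRT.

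**Conclusion.** The point holds in a limited form. The contrast named for changing biomarkers cannot, from day 8 on, divide a change among VPA, capecitabine, radiotherapy and time. A randomised contrast that could do so is available from samples already listed. The gap is greatest for capecitabine, which has neither an exposure correlation nor a radiotherapy-free sample, and for surgical tissue, taken about 40 days after VPA ends.

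The size is conditional: 26% to 94% at 21 patients and 48% to 99.9% at 43, for assumed common shifts of 0.3 to 0.8 SD, and only if a change is read as a drug effect. With no common shift the two tests behave alike at about 5%. The availability of blood controls rests on the sampling sentence carrying no arm restriction. The schedule figure is not visible in the text at hand. The TRG1 comparison is not touched, so this is a worthwhile clarification, not a threat to the trial's main result.

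**What to change.** In 'Statistical analysis of phase II', or in the SAP if it elaborates that section:

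1. State that post-baseline biomarker values, adjusted for baseline (ANCOVA or a rank equivalent), are compared between randomised groups, VPA yes/no and capecitabine yes/no, at the shared blood times and for surgical tissue.
2. Keep within-arm before/after results as description.
3. Label the day -4 tumour change, sampled only in VPA patients, as free of radiotherapy but without a concurrent control.
4. Retain the correlation of VPA serum level with PBMC acetylation as a supporting analysis.

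One limit should be stated with the tissue comparison. Patients with complete regression have no residual tumour to assay. At the planned TRG1 rates that would leave about 43 × 0.95 = 41 against 43 × 0.80 = 34 tumour samples, so this contrast is not fully protected by randomisation. The blood comparisons do not share this problem.

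The cost is wording, a little more analysis and lower precision than a paired test (about 0.60 against 0.43 SD detectable at 43 per side). No further patients or samples are needed, and the analysis stays exploratory.
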